#### Stroke Adapted Sickness Impact Profile 30 (SA-SIP30)

The Stroke Adapted Sickness Impact Profile measures sickness specific quality of life in stroke patients and is a modified version of the 136-item SIP. This instrument was developed primarily to overcome the length of the original SIP, which is its major disadvantage. The SA-SIP30 is a 30-question instrument with eight subgroups, created by eliminating the most irrelevant questions from the initial test. The higher the score the lesser the quality of life after stroke[12].

#### Barthel index (BI)

The Barthel index is a generic questionnaire which consists of 10 items measuring activities of daily life (ADL) and mobility. A high score on the Barthel index corresponds with a high degree of independence concerning the activities of daily life[13,14].

#### Frenchay Activities Index (FAI)

The Frenchay Activities Index is a stroke specific instrument to assess functional status. The FAI is comprised of 15 items, each concerning an activity that requires some decision making and organisation on the part of the patient[15].

#### Modified Rankin Scale (MRS)

The Modified Rankin Scale is a widely used instrument that measures levels of handicap. It defines 6 levels of disability, ranging from 0 (no symptom) to 5 (severe disability, bedridden, incontinent and receiving constant nursing care and attention)[16].

#### Mini Mental State Examination (MMSE)

The mini mental state examination is the most widely used instrument to screen for cognitive dysfunction. The MMSE assesses orientation, memory, attention, language, and constructive functions. The MMSE consists of 20 items with a maximal total score of 30[17].

#### Apraxia Test (AT)

The Apraxia Test is a short and easy test to measure the degree of apraxia in stroke patients. It consists of two subtests, one designed to evaluate the use of objects and another to evaluate the ability to imitate gestures. The maximum score for the total test is 90[18].

#### Star Cancellation Test (SCT)

The Star Cancellation Test is the most sensitive single test for neglect. Depending on the number of missed stars the magnitude of neglect can be measured[19].

#### Hospital Anxiety and Depression Scale (HADS)

The Hospital Anxiety and Depression scale was developed to identify anxiety and depression among patients. It is divided into an anxiety subscale and a depression subscale, each containing seven intermingled items. The maximum score is 47. The higher the score the greater the possibility of anxiety or depression[20].

#### Satisfaction with Stroke Care Questionnaire 19 (SSCQ-19)

The 19-item version of the satisfaction with stroke care questionnaire is comprised of eight items measuring satisfaction with inpatient stroke care, and eleven items measuring satisfaction with stroke care after discharge[21].

#### Caregivers Strain Index (CSI)

The Caregivers Strain Index is a 13-item instrument that ascertains strain on care givers across domains of employment, finances, physical health, and social relationships. A positive answer to 7 or more of the items reflects a more than average strain on caregivers[22].

#### The National Institute of Health Stroke Scale (NIHSS)

The National Institute of Health Stroke Scale provides a measure of severity of symptoms associated with cerebral strokes. It measures level of consciousness, visual fields, motor response, sensation, language and neglect on weighted scales. The NIHSS can be used with persons of all ages, including geriatric patients, who have had a stroke[23]. The higher the score, the more severely affected is the patient.

#### European Quality of Life instrument (EuroQol)

The European Quality of life instrument (EuroQol) is a well-known generic instrument measuring health-related quality of life. It includes 5 dimensions (mobility, self-care, daily activities, pain/discomfort and anxiety/depression) and a visual analogue scale that evaluates patients' perceived health status[24]. Each dimension can be rated at three levels: no problems, some problems and major problems. The 5 dimensions can be summarized in a health state.

#### Cost Questionnaire

We will assess intervention costs, healthcare costs, patient and family costs, and costs outside the healthcare sector. For this study we will develop a cost questionnaire especially designed for this group, based on existing questionnaires[28,29], which identify all relevant costs aspects.

### Effect analysis

For the analyses we will use SPSS statistical software and Excel (for the Bootstraps). Missing data on the item level will be handled using SPSS missing value analysis. If considerable data are missing related to specific instruments, imputation will be considered.

A baseline analysis will be performed to examine the comparability of groups at baseline for both costs and outcomes. If necessary, methods will be applied to correct for differences in baseline[30]. A Kolmogorov-Smirnov test will be performed to investigate whether the data are normally distributed. If the data are distributed normally, our primary analysis will start with a t-test. If data are skewed, the primary analysis will be based on a non-parametric test for assessing two independent samples, i.e. a Mann-Whitney U test.

As it is known that in non-randomised comparative studies, variations in case mix between centres can influence the interpretation of outcome data[31], we would like to explore this in further analysis. Therefore, for each of the data sets collected at all measurement points, differences in outcome variable between the 2 regions will be tested using multiple MANCOVAs, entering various indicators of case mix as co-variates, i.e. age, gender, stroke severity. In addition, information on possible confounding factors and effect modifiers will be collected and analysed.

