**Methods/design:**

The design involves a non-randomised comparative trial for two groups. Participants are followed for 6 months from the time of stroke. The intervention consists of a redesigned care pathway for stroke patients. In this care pathway, patients are discharged from hospital to a nursing home within 5 days, in comparison with 12 days in the usual situation. In the nursing home a structured assessment takes place, aimed at planning adequate rehabilitation. People in the control group receive the usual care. The main outcome measures of the effect evaluation are quality of life and daily functioning. In addition, an economic evaluation will be performed from a societal perspective. A process evaluation will be carried out to evaluate the feasibility of the intervention as well as the experiences and opinions of patients and professionals.

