### Effect evaluation

The primary outcome measures of the effect evaluation are quality of life and activities of daily life (ADL). Quality of life is measured by means of the Stroke Adapted Sickness Impact Profile 30 (SA-SIP 30)[12] and ADL by means of the Barthel index (BI)[13,14].

Secondary outcome measures are: instrumental activities of daily living (IADL) measured by means of the Frenchay Activity Index (FAI)[15], handicap measured by means of the Modified Rankin Scale (MRS)[16]. Cognitive functioning is measured by means of Mini Mental State Examination (MMSE)[17], Apraxia Test (AT)[18] and Star Cancellation Test (SCT)[19]. Anxiety and depression are measured by the Hospital Anxiety and Depression Scale (HADS)[20] and the patients' satisfaction with stroke care is measured by means of the Satisfaction with Stroke Care Questionnaire (SASQ-19)[21]. The strain on caregivers is measured by the Caregivers Strain Index (CSI)[22].

Other secondary outcome measures are medical complications occurring within 3 months after stroke. The following diagnoses are regarded as medical complications: a new stroke, epileptic seizures, pneumonia, urinary tract infections, fractures, bedsores, myocardial infarct, heart failure and atrial fibrillation. The data on medical complications will be collected from the patients' files.

Besides the primary and secondary outcome measures we assess some background variables which are considered to be predictors, confounders or effect modifiers. The following personal characteristics are assessed: age, sex, socio-economic status, risk factors, co-morbidity, stroke location and stroke severity measured by the National Institute of Health Stroke Scale (NIHSS)[23]. All background variables are measured at baseline.

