Despite the usual skewness in the distribution of costs, arithmetic means are generally considered the most appropriate measure to describe cost data[36,37]. Therefore, arithmetic means (and standard deviations) will be presented. In case cost data are skewed, non-parametric bootstrapping will be used to test for statistical differences in costs between the intervention and control group. Non-parametric bootstrapping is a method based on random sampling with replacement based on the individual data of the participants[38]. The bootstrap replication will be used to calculate 95% confidence intervals around the costs (95% CI), based on the 2.5 th and 97.5 th percentiles. If cost data are distributed normally, t-tests will be used.

The incremental cost effectiveness ratio (ICER) will be determined on the basis of incremental costs and effects of the intervention compared to care as usual. The cost effectiveness ratio will be stated in terms of costs per outcome rate; the cost utility ratio will focus on the net cost per QALY gained.

The ICER will be calculated as follows. ICER = (Ci-Cc)/(Ei-Ec), where Ci represents the total costs of the intervention group at the 26-weeks follow-up, Cc the total costs of the care as usual group at the 26-weeks follow-up, Ei the effects at the 6-month follow-up for the intervention group and Ec the effect at the 26-weeks follow-up for the care as usual group. The robustness of the ICER will be checked by non-parametric bootstrapping (1000 times). Bootstrap simulations will also be conducted in order to quantify the uncertainty around the ICER, yielding information about the joint distribution of cost and effect differences. The bootstrapped cost-effectiveness ratio will be plotted subsequently in a cost-effectiveness plane, in which the vertical line reflects the difference in costs and the horizontal line reflects the difference in effectiveness.

The choice of treatment depends on the maximum amount of money that society is prepared to pay for a gain in effectiveness, which is called the ceiling ratio. Therefore, the bootstrapped ICERs will also be depicted in a cost effectiveness acceptability curve showing the probability that the intervention care is cost effective using a range of ceiling ratios.

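### The primary comparison of two non-randomised regions is an unadjusted test picked by a normality check, and no case-mix adjustment is stated for costs, QALYs or the ICER

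*Protocol article*

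**What the plan says.** The abstract of the protocol article sets out the design: "The design involves a non-randomised comparative trial for two groups". Each arm is one regional stroke service with one hospital.

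The Effect analysis section then proceeds in this order:

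- Baseline check: "A baseline analysis will be performed to examine the comparability of groups at baseline for both costs and outcomes". Differences are to be corrected where that proves necessary. A reference is cited, but the text gives no trigger or covariates and does not say which analysis would be corrected.
- Choice of test: "A Kolmogorov-Smirnov test will be performed to investigate whether the data are normally distributed".
- Primary analysis, first branch: "If the data are distributed normally, our primary analysis will start with a t-test".
- Primary analysis, second branch: "If data are skewed, the primary analysis will be based on a non-parametric test for assessing two independent samples, i.e. a Mann-Whitney U test".
- Case mix: the authors accept that in non-randomised studies "variations in case mix between centres can influence the interpretation of outcome data", and say they wish to explore this further. They then commit to several MANCOVAs at every measurement point, with age, gender and stroke severity as covariates. A last sentence says that other confounders and effect modifiers will be gathered and analysed, without saying how.

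Under Effect evaluation, "we assess some background variables which are considered to be predictors, confounders or effect modifiers". All are recorded at baseline, and they include NIHSS severity, co-morbidity and socio-economic status as well as age and sex.

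On costs, the Economic analysis section says: "In case cost data are skewed, non-parametric bootstrapping will be used to test for statistical differences in costs between the intervention and control group". If cost data are normal, t-tests are used. The ICER is the difference in costs over the difference in effects between the groups, with 1000 bootstrap replications. No case-mix adjustment is mentioned in that section.

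**The concern.** Region and treatment coincide in this design, so a crude difference mixes the care pathway with any difference in age, severity or co-morbidity between the two hospitals' patients. The plan recognises this and collects variables that could address it, but the analysis it calls primary uses none of them.

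Some imbalance is plausible even if the catchment populations are alike. The Study population section excludes patients who go home within a few days and those whose complications prolong the hospital stay. Both depend on decisions made after admission, and discharge practice is what differs between the regions.

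The normality check adds a second weakness. A t-test compares means and a Mann-Whitney test compares rank distributions, so what the primary analysis tests is settled only after the data are seen.

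Much rests on the result: the Discussion says that proven cost effectiveness would make a clear case for adopting the pathway in usual care.

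**Working it through.** **1. Can the promised baseline check be done?** Table 1 sets the timing of each instrument.

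| Measure | Role | Value at T0? |
|---|---|---|
| SA-SIP30 | primary outcome; outcome of the cost-effectiveness analysis | no (12 and 26 weeks) |
| Barthel index | primary outcome | yes |
| EQ-5D | source of QALYs | no (12 and 26 weeks) |
| Cost questionnaire | costs | no (12 and 26 weeks) |

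Of these four, only the Barthel can be compared or corrected on its own baseline. For the rest, adjustment has to use other baseline variables such as NIHSS, age, T0 Barthel or T0 Rankin.

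**2. The plan's own figure, in SD units.** The Sample Size section gives 111 per group, 80% power and alpha 0.05, with no SD and no sidedness. Assuming a two-sided test:

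- standard error of a mean difference = √(2/111) = 0.134 SD
- detectable difference = (1.960 + 0.842) × 0.134 = 0.376 SD

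So the planned utility difference of 0.11 corresponds to 0.376 SD. This agrees with 111 per group only because the missing SD (0.11/0.376 = 0.2925) is solved from it. It serves as a yardstick, not as an independent reproduction.

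**3. False positives of the crude test.** Let *b* be the shift in the outcome, in SD units, that comes from case mix alone, with no true effect. The documents give no value for *b*, so a range is assumed. The chance that the unadjusted two-sided test is significant is

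P = 1 − Φ(1.96 − b/0.134) + Φ(−1.96 − b/0.134)

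| b (SD, assumed) | b/0.134 | P, 111 per group |
|---|---|---|
| 0 | 0 | 5% |
| 0.1 | 0.745 | 12% |
| 0.2 | 1.490 | 32% |
| 0.3 | 2.235 | 61% |
| 0.376 | 2.80 | 80% |

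The last row is the planned effect produced wholly by case mix. With 104 per group (139 × 0.75), the rates for 0.1, 0.2 and 0.3 SD are 11%, 30% and 58%.

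**4. What adjustment does to a measured confounder.** This was simulated with 111 per group, 4,000 runs per scenario and no true effect. One baseline covariate differs between regions by D SD and correlates r with the outcome, so b = D × r. Both D and r are assumptions.

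| D | r | b | Crude t-test | Covariate-adjusted |
|---|---|---|---|---|
| 0.2 | 0.3 | 0.06 | 7% | 5.1% |
| 0.2 | 0.5 | 0.10 | 12% | 5.0% |
| 0.3 | 0.5 | 0.15 | 20% | 5.6% |
| 0.5 | 0.6 | 0.30 | 62% | 4.5% |

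Over all scenarios with D from 0.2 to 0.5 and r from 0.3 to 0.6, the crude test rejected in 7% to 62% of runs and the adjusted model in 4.5% to 5.6%. The simulation has a single confounder, measured without error and correctly modelled, so it shows the best that adjustment can do.

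**5. The ICER.** Resampling patients within two unbalanced groups reproduces the imbalance in each replicate. The bootstrap therefore describes sampling uncertainty around a biased centre and does not remove the bias.

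**The case against.** The plan does not ignore adjustment. It allows a baseline correction, which follows a comparison that covers costs as well as outcomes, and the method may lie in the cited reference or in a fuller document that is not shown. The MANCOVAs are a commitment, and the t-test is only where the analysis starts. The remaining confounders are to be analysed too, and the Discussion admits possible bias from non-randomisation.

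Most of this is fair, and it rules out several stronger readings:

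- A reader might infer that no adjustment is planned, or that confounding is certain to reach the headline result. The text supports neither: adjustment is planned, but in a conditional or secondary role.
- A reader might infer that the sign of the effect or the ICER will be wrong. The documents give no imbalance and no covariate slope from which to derive that.
- A reader might infer that a Mann-Whitney result would undermine the ICER. Nothing passes that test into the ICER, which has its own group differences and bootstrap.
- A reader might expect a stated gain in power from adjustment. No SD is given, and the usual variance-reduction formula assumes balanced covariates, which is the very thing in doubt here.

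What the objection does not reach is the hierarchy. The article itself assigns the label of primary to a test without covariates, so this is a stated choice and not a detail left to an analysis plan. A correction applied only if needed, with neither trigger nor target in the text, does not change that choice.

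**Conclusion.** The point holds for the primary effect analysis and for the economic analysis. Followed as written, the plan reports as primary a comparison that measured case mix can bias, and it builds the ICER from group differences with no case-mix adjustment stated.

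The size of the bias cannot be known from the documents. The figure of about 12% to 61% false positives rests on an assumed shift of 0.1 to 0.3 SD, no true effect, 111 per group and a two-sided 5% test. It shows that shifts smaller than the planned effect are enough to matter; it does not predict what this study will find.

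**What to change.** - Make the primary analysis a pre-specified regression of 26-week SA-SIP30 and Barthel on region, adjusted for age, sex, NIHSS, T0 Barthel, co-morbidity and socio-economic status. Use bootstrap confidence intervals if residuals are skewed.
- Drop the Kolmogorov-Smirnov switch and report the crude tests as descriptive.
- Carry the same covariates into the incremental costs, the QALYs and every replicate of the ICER bootstrap.
- T0 falls within one week of stroke, while the intervention transfers patients after at most 5 days, so some T0 Barthel scores may follow transfer. Flag these, or handle them in a sensitivity analysis. The timing of T0 need not change; that would alter data collection in a study with a retrospective part.

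The cost is revised analysis wording and a little more analysis work, since every covariate is already collected. Unmeasured differences between the regions will remain, and the report should say so.

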### Sample Size

The primary goal of this study is to achieve cost reduction without loss of quality of life. Based on an earlier study among stroke patients[10], we estimate a difference in utilities indicating health related quality of life between the 2 regions. In this earlier study by Olsen, the utility difference based on the EuroQol was 0.11. Based on a power of 80%, alpha 0.05, our study will need a sample size of 111 participants per group.

We expect a 25% drop-out of patients between inclusion and the follow-up meeting 26 weeks later, due to premature termination of the trial participation, inability to cooperate in the trial, or mortality[11]. To correct for this expected drop-out, the number of patients included will be increased to 139 participants per group.

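### Adjusting for case mix by separate MANCOVAs at each visit leaves earlier scores unused and designates no adjusted 26-week difference for the primary outcomes; a repeated-measures model would be a cheap improvement

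*Protocol article*

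**What the plan says.** Under Effect analysis, the protocol article makes an unadjusted two-group test primary: "If the data are distributed normally, our primary analysis will start with a t-test", or, for skewed data, "a non-parametric test for assessing two independent samples, i.e. a Mann-Whitney U test". Case mix comes afterwards, introduced by "we would like to explore this in further analysis". The method is then fixed: "differences in outcome variable between the 2 regions will be tested using multiple MANCOVAs". This is done separately on the data of every measurement point, and the covariates named are age, gender and stroke severity.

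The same section sends missing items to SPSS missing value analysis and leaves imputation as a possibility if much of an instrument is missing. It also allows unspecified methods for correcting baseline differences where needed, and says that confounders and effect modifiers will be analysed. It does not say which outcomes share a MANCOVA.

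Table 1 (Instruments) schedules the Barthel index at T0 and at 4, 12 and 26 weeks, and the SA-SIP30 at 12 and 26 weeks only. These are the two primary outcomes of the effect evaluation. On attrition, Sample Size says: "We expect a 25% drop-out of patients between inclusion and the follow-up meeting 26 weeks later", and gives as reasons withdrawal, inability to cooperate, and death.

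**The concern.** The Discussion concedes that non-randomisation may bias the comparison of the two regions. A case-mix-adjusted result is therefore the one that readers will lean on for research question 1. An analysis confined to one visit's data has three consequences.

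- A patient seen at 12 weeks and then lost is absent from the 26-week comparison, unless the missing score is imputed.
- A patient missing any outcome that enters a given MANCOVA falls out of that MANCOVA, again unless imputed.
- The plan announces tests at each visit, but does not say which adjusted difference, at which visit, answers the question for the SA-SIP30 and the Barthel index.

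Some of the expected loss is related to how patients are doing. If that relation differs between the regions, a comparison of completers can be distorted.

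**Working it through.** **Inputs from the protocol article.** 111 per group, raised to 139; 25% loss by 26 weeks; utility difference 0.11; power 80%; alpha 0.05 (Sample Size). Visit schedule from Table 1.

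**Step 1: the plan's own figures.** The 111 cannot be reproduced from the text alone, because no SD is given. With two-sided alpha 0.05 and the normal approximation, the implied SD is 0.11 / [(1.960 + 0.842) × √(2/111)] = 0.2925, a standardised effect of 0.11/0.2925 = 0.376. The 139 is 111 × 1.25 = 138.75, rounded up. Expected completers are 139 × 0.75 = 104.25 per arm. At 0.376 SD that gives power Φ(0.376 × √(104.25/2) − 1.960) = Φ(0.755) = 77.5%. This effect size belongs to the EQ-5D utility and serves only as a yardstick for the two primary outcomes.

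**Step 2: precision recovered from the 12-week scores.** With n2 patients per arm seen at 12 weeks, n3 at 26 weeks and correlation ρ between the two scores, a likelihood-based model has an effective 26-week sample of n3 / [1 − ρ²(1 − n3/n2)]. Assumed: 10% to 20% already lost by 12 weeks, ρ from 0.5 to 0.8.

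- Most favourable (10% lost, ρ = 0.8): n2 = 125.1; 104.25 / [1 − 0.64 × 0.1667] = 116.7; power 82%.
- Least favourable (20% lost, ρ = 0.5): n2 = 111.2; 104.25 / [1 − 0.25 × 0.0625] = 105.9; power 78%.

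So 104 becomes 106 to 117 per arm.

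**Step 3: loss within one MANCOVA if nothing is imputed.** With k outcomes, each missing independently with probability m among completers (assumed), 104.25 × (1 − m)^k patients per arm remain. For the two primary outcomes alone:

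- m = 2%: 104.25 × 0.9604 = 100.1.
- m = 5%: 104.25 × 0.9025 = 94.1.

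**Step 4: bias from dropout.** Simulation with 4,000 replicates and 139 per arm; normal scores; true difference 0.376 SD at both visits; 10% lost at random before 12 weeks; later dropout depending on the 12-week score (logistic slope 1 per SD), or occurring at random in the region where no dependence is assumed. About 100 per arm complete. No covariates were used. Ranges are over ρ = 0.5, 0.7 and 0.8.

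- Dependence in one region only: completers-only bias −0.10 to −0.16 SD, that is 0.099/0.376 = 26% to 0.155/0.376 = 41% of the true difference; likelihood-based bias below 0.01 SD.
- Same dependence in both regions: completers-only bias −0.02 to −0.03 SD; likelihood-based bias again below 0.01 SD.

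The sign follows from how the scenario was set up and is not a prediction for this trial.

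**The case against.** Several arguments against the point have force.

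- **Deletion is not a stated rule.** A reader might infer that the plan drops every patient with a missing outcome. It does not say so. Deletion is the usual software default, and imputation is left open; its trigger and method may properly stand in an analysis plan that is not shown.
- **MANCOVA does yield adjusted differences.** A reader might infer that no adjusted SA-SIP30 or Barthel difference will exist. The per-outcome contrasts supply them. What is missing is a designated one.
- **The loss need not be severe.** Putting all nine effect instruments of the 26-week visit into one MANCOVA would leave 104.25 × 0.98⁹ = 87 or 104.25 × 0.95⁹ = 66 per arm. The article speaks of multiple MANCOVAs and does not group the outcomes, and instruments at one visit tend to be missing together. Those figures are a worst case and are not relied on.
- **Other adjustment is allowed.** Unspecified baseline correction is permitted, so the MANCOVAs are the only specified case-mix adjustment, not the only possible one.
- **The remedy has limits.** A linear mixed model also rests on normality, does not deal with deaths, and gains little for an SA-SIP30 with two visits and no baseline.
- **These are follow-on analyses.** Replacing them leaves the unadjusted primary test in place.

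All of this narrows the point. What stands is that a visit-by-visit method ignores repeated scores already scheduled, in a study that expects a quarter of its patients to be lost, and that no adjusted 26-week estimate is named.

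**Conclusion.** The point holds as a cheap improvement, not as a flaw that invalidates the plan. The precision gain is modest (104 to between 106 and 117 per arm) and depends on the assumed correlation and timing of loss. The main benefit is protection against score-dependent dropout that differs by region: 0.10 to 0.16 SD in the assumed one-region scenario, but only 0.02 to 0.03 SD if the mechanism is shared. The documents give no evidence as to which applies. Adjustment for age, gender and stroke severity might remove part of that bias, since the simulation had no covariates. The likelihood-based result assumes that dropout is missing at random given the observed scores. That assumption does not cover death, which is part of the expected 25%.

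**What to change.** For the two primary outcomes, replace the MANCOVAs with one covariate-adjusted linear mixed model each:

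- fixed effects for region, visit, region-by-visit, age, sex and NIHSS;
- Barthel index at 4, 12 and 26 weeks, with baseline Barthel as a covariate;
- SA-SIP30 at 12 and 26 weeks.

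Name the 26-week regional difference with its 95% CI as the main adjusted estimate. This matches the time point at which the Economic analysis section takes effects, and it serves research question 1 best if the model is not left as mere further exploration. Use bootstrap or robust intervals if scores are skewed. State how deaths are handled, for example an estimate among survivors plus a sensitivity analysis that assigns death a score; otherwise the model extrapolates scores beyond death. Analyse each secondary outcome in its own adjusted model, including the Caregivers Strain Index, which exists only where there is a caregiver.

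Cost: a change of analysis wording, no new data, and SPSS, already the chosen software, can fit the model. The downside is somewhat more analysis work and reliance on a missing-at-random assumption, which should be stated.

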### Instruments

The instruments used in this study are shown in Table 1

**Table 1 T1:** Overview of instruments per time point

	Time after stroke			
Instrument	T0	T1	T2	T3
	< 1 week	4 Weeks	12 Weeks	26 Weeks
SA-SIP30			X	X
Barthel index	X	X	X	X
Frenchay Activities Index	X			X
Modified Rankin Scale	X	X	X	X
Mini Mental State Examination	X			X
Apraxia Test	X			X
Star Cancellation Test	X			X
Hospital Anxiety and Depression scale		X		X
SASC-19	After every discharge			
Caregivers Strain Index				X
EQ-5D			X	X
Cost Questionnaire			X	X

Instruments used for the screening process, the clinical outcome assessment and the economic evaluation. In Table 1 an overview of all assessments per time point is shown.

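### The only named case-mix model omits baseline Barthel and four recorded background variables, and no other sentence commits them to an analysis

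*Protocol article*

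**What the plan says.** Under Effect analysis, the first comparison of the regions is unadjusted: "If the data are distributed normally, our primary analysis will start with a t-test", with a Mann-Whitney U test if the data are skewed. Case mix comes afterwards and is introduced with the words "we would like to explore this in further analysis". The model for it is a set of MANCOVAs, "entering various indicators of case mix as co-variates, i.e. age, gender, stroke severity".

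Two other sentences in the section bear on confounding. After a baseline comparison of the groups on outcomes and costs, the article says "If necessary, methods will be applied to correct for differences in baseline". At the end it says "In addition, information on possible confounding factors and effect modifiers will be collected and analysed".

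Under Effect evaluation, the background variables that may predict, confound or modify the effect are "age, sex, socio-economic status, risk factors, co-morbidity, stroke location and stroke severity measured by the National Institute of Health Stroke Scale", all taken at baseline. Table 1 ("Overview of instruments per time point") schedules Barthel, Frenchay, Rankin, MMSE, the Apraxia Test and the Star Cancellation Test at T0. SA-SIP30, EQ-5D and the cost questionnaire start at 12 weeks.

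**The concern.** Region determines treatment, so any difference in patient mix between the regions is mixed with the treatment effect. The Discussion names non-randomisation as a weak point, and the Effect analysis section accepts that case mix can distort the comparison. Yet the covariate set is narrower than the article's own list of possible confounders, and it leaves out the starting value of one of the two primary outcomes.

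Two things are at stake. If the regions differ on an omitted prognostic variable after allowing for age, sex and NIHSS, the estimated effect is biased by that difference. Even without such a difference, leaving out a strong predictor widens the confidence interval. The variables are already being recorded, so both losses are avoidable.

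**Working it through.** **Text check: which recorded variables reach the named model?**

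| Recorded at baseline | In the named model? |
|---|---|
| Age, sex, NIHSS | Yes |
| Stroke location, co-morbidity, socio-economic status, risk factors | No |
| T0 Barthel (primary outcome) | No |
| T0 Rankin, MMSE, Frenchay, Apraxia, Star Cancellation | No |
| SA-SIP30, EQ-5D, cost questionnaire | No T0 value exists |

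The last row limits what the conditional baseline correction can do. Of the two primary outcomes, only Barthel has a T0 value to correct for. For SA-SIP30, utilities and questionnaire costs, the other baseline variables are the only means of adjustment.

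**The plan's own figure.** The article gives no figure for the effect of adjustment. I use its 111 per group (Sample Size section) only as a reference size. No SD is stated. With a difference of 0.11, two-sided 5% and 80% power, 111 per group implies SD = 0.11 × √(111/2) / (1.960 + 0.842) = 0.2925. So 111 is plausible but cannot be checked independently.

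**Precision.** Let r be the partial correlation of T0 Barthel with the outcome, given age, sex and NIHSS. The documents do not give r, so I assume 0.3 to 0.5. Adding T0 Barthel multiplies the residual variance by 1 − r².

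| r | 1 − r² | Variance removed | Patients per group for the same precision as 111 (rounded up) |
|---|---|---|---|
| 0.3 | 0.91 | 9% | 102 |
| 0.4 | 0.84 | 16% | 94 |
| 0.5 | 0.75 | 25% | 84 |

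Imbalance takes back a little of this. If the regions differ by d SD on T0 Barthel, the variance of the region effect is multiplied by 1 + d²/4, which is 1.01 at d = 0.2.

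**Bias.** Let d be the between-region difference in T0 Barthel that remains after age, sex and NIHSS, in SD units. It is also not given; I assume 0.1 to 0.2. Omitting T0 Barthel then leaves a bias of r × d outcome SDs. With standard error √(2/111) = 0.134 SD, the chance of a false positive at a nominal two-sided 5% is:

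| r | d | Bias (SD) | Type I error |
|---|---|---|---|
| 0.3 | 0.1 | 0.03 | 5.6% |
| 0.3 | 0.2 | 0.06 | 7.3% |
| 0.5 | 0.1 | 0.05 | 6.6% |
| 0.5 | 0.2 | 0.10 | 11.6% |

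**Why the correlation must be partial.** NIHSS is already in the model and overlaps with Barthel. For illustration, assume absolute correlations of 0.5 between NIHSS and outcome and 0.65 between NIHSS and T0 Barthel. A raw T0-to-26-week correlation of 0.5 becomes (0.5 − 0.5 × 0.65) / √((1 − 0.25)(1 − 0.4225)) = 0.175/0.658 = 0.27. A raw 0.7 becomes 0.375/0.658 = 0.57. The variance removed is then about 7 to 32%, not the 25 to 49% that the raw values suggest.

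**Timing of T0.** Table 1 puts T0 within the first week. The intervention pathway moves patients to the nursing home after at most 5 days, while the mean hospital stay in the control region is 10 days. A T0 score from the end of that week could therefore follow transfer, and mainly in the intervention region.

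**The case against.** The strongest reply is that the article does not confine itself to three covariates. The word various before the list suggests illustration. The baseline correction most naturally reaches T0 Barthel, and the closing sentence on confounders matches the list under Effect evaluation. A condensed article may also leave the final list to an analysis plan.

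Part of this stands. A reader might infer that the plan ignores all other confounders or contradicts itself; the two sentences rule that out. But one is conditional and names neither method nor variable, and the other does not say that anything enters a model. The article did choose to state a covariate list, and worded it as complete.

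A reader might also infer that covariate adjustment is the only protection against confounding. It is not: the regions share eligibility criteria, and the control region was chosen as comparable.

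A third tempting inference is that the omission costs up to half the residual variance, or biases the result by about a third of the effect the trial was sized for. The documents support neither. The first uses a raw correlation although NIHSS is already in the model. The second sets a Barthel bias against an effect size derived from EuroQol utilities.

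Two objections bear on the remedy, and both stand. A T0 Barthel taken after transfer may already reflect the intervention, so adjusting for it could remove part of the effect. And enlarging a model that is only exploratory would leave the unadjusted primary test as it is.

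**Conclusion.** The point holds in a limited form. The one named case-mix model omits the baseline value of a primary outcome and four variables that the article itself treats as potentially confounding, and no other sentence commits them to an analysis. Avoidable confounding and residual variance remain.

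The direction is firm: any non-zero partial correlation lowers variance, and any remaining imbalance leaves bias. The size is not. A 9 to 25% cut in residual variance and 0.03 to 0.10 SD of bias rest wholly on assumed partial correlations of 0.3 to 0.5 and remaining imbalances of 0.1 to 0.2 SD. The case is clearest for Barthel. For SA-SIP30, T0 Barthel would serve as a prognostic stand-in, because that scale has no baseline.

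The larger weakness in the same section is that adjustment of any kind is secondary to an unadjusted test. A longer covariate list helps fully only if the adjusted comparison becomes the main one.

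**What to change.** Prespecify one adjusted between-region model and report it as the main comparison, whatever a baseline test shows. Its covariates should be age, sex, NIHSS, socio-economic status, co-morbidity, stroke location and T0 Barthel. State how risk factors are handled, for instance within the co-morbidity measure, or give the reason for leaving them out. Use the same set for SA-SIP30, Barthel, QALYs and costs.

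Record the date of each T0 assessment. Use T0 Barthel as a covariate only where it was recorded before transfer to the nursing home, and add a sensitivity analysis without it. T0 Rankin and T0 MMSE are optional, because they overlap with NIHSS and Barthel.

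The cost is small. The variables are already collected, and about 208 expected completers (2 × 139 × 0.75) can carry a model of this size. The downsides are slightly more analysis work and possible loss of patients with incomplete covariates, so the plan should say how missing covariate values are handled.
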